## Assignment of interventions: blinding

### Who will be blinded {17a}

This is a double-blind study. Both the participants and the clinicians will be blind to the allocation of groups and order of intervention. The hearing aid settings and real-ear measurements will be stored anonymously so that the clinician is unable to determine what fitting process was used. The participants and clinicians will be aware of the intervention strategy at the fitting process (in-clinic or remote), which occurs prior to group allocation and blinding.

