#### Initial in-clinic hearing aid fitting

For the initial in-clinic hearing aid fitting, participants will be fit binaurally with premium-level, rechargeable, receiver-in-the-canal hearing aids. The receiver and dome configuration will be chosen using standard clinical procedures and be consistent for each participant for the duration of the study. The hearing aids will be programmed through the manufacturer’s software to 100% acclimatisation using the National Acoustics Laboratory Non-Linear 2 (NAL-NL2) prescription targets for long-term hearing aid wearers.

REAR will be verified using a Natus Aurical Freefit and Otometrics Otosuite PMM module, with the gain settings adjusted through hearing aid software to meet NAL-NL2 targets for soft (55 dB), medium (65 dB), and loud (75 dB) stimuli using the International Speech Test Signal. On-ear measurement of maximum power output will be measured at 85 dB to ensure estimated uncomfortable loudness levels are not exceeded.

Where hearing aid programming features are available for an in-clinic session but are not available for a remote session, these will be removed from the in-clinic fitting protocol to maintain blinding for the clinicians performing the follow-up appointments.

Hearing aid settings will be optimised using subjective participant feedback to balance overall volume, perceived sound quality, and perception of own voice/occlusion. This process will follow an interview-style approach, with the participant asked to comment on each component and the clinician making small adjustments to the hearing aid settings until the participant is satisfied with the sound. The hearing aid setting will then be stored and the hearing aids retained at the clinic.

Participants will be required to have an app installed on their smartphone or tablet before the remote hearing aid fitting appointment. They will be guided through this process at the end of the initial in-clinic fitting appointment.

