#### Initial remote hearing aid fitting

Approximately 2 weeks after the in-clinic hearing aid fitting, a remote hearing aid fitting appointment will take place. The time interval is to allow participants’ memory of the sound of the in-clinic programming to decay so that it is less likely to influence the remote fitting. The same hearing aids used at the in-clinic hearing aid fitting will be reset in-clinic and programmed through hearing aid software to 100% acclimatisation using NAL-NL2 prescription targets for long-term hearing aid wearers. The hearing aids will be programmed to allow for a remote hearing aid connection.

The hearing aids will be sent to the participant via courier.

At the scheduled hearing aid fitting appointment time, the clinician will telephone the participant to confirm the app installation and Bluetooth pairing was successful. The participant and clinician will then connect through the app for a remote support session.

Remote support allows an audio–video link between the participant and clinician. The clinician will connect to the participant’s hearing aids through a Bluetooth connection with the participant’s smartphone or tablet.

When both the participant and the clinician are connected to the remote support appointment, the clinician will perform proxy verification measurements through the hearing aid manufacturer software.

Hearing aid settings will be optimised using subjective participant feedback to balance overall volume, perceived sound quality, and perception of own voice/occlusion. This process will follow an interview-style approach, with the participant asked to comment on each component and the clinician making small adjustments to the hearing aid settings until the participant is happy with the sound.

The hearing aid settings will be saved, and the participant will return the hearing aids to the clinic through return-post courier.

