### Concealment mechanism {16b}

Participants are assigned to one of the intervention groups but the group is concealed from them. They will not be aware of which fitting method they are trialling at any stage. Clinicians are not aware of which groups the participants have been assigned. A research assistant will allocate participants and will deidentify the hearing aid fitting files within Noah software. Each participant will have 2 hearing aid files (intervention A and B), and it will not be apparent to the researcher which intervention setting is being used at any time. The researcher will not know which group a participant is allocated by the research assistance until after the research is complete, at which point the research assistant will share the electronic records.

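### Anonymous storage of the settings does not secure blinding of the clinician whose gain adjustments feed the primary outcome

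*Protocol article*

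**What the plan says.** Under Who will be blinded {17a}, the article makes a positive claim and names its mechanism: "The hearing aid settings and real-ear measurements will be stored anonymously so that the clinician is unable to determine what fitting process was used". The same section concedes that "The participants and clinicians will be aware of the intervention strategy at the fitting process (in-clinic or remote), which occurs prior to group allocation" and, as the sentence goes on, prior to blinding.

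Two further safeguards are described:

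- **Concealment mechanism {16b}:** a research assistant allocates participants and "will deidentify the hearing aid fitting files within Noah software". It adds: "Each participant will have 2 hearing aid files (intervention A and B), and it will not be apparent to the researcher which intervention setting" is in use at any time.
- **Initial in-clinic hearing aid fitting:** where a programming feature cannot be used in a remote session, such features are taken out. In the article's words, "these will be removed from the in-clinic fitting protocol to maintain blinding for the clinicians performing the follow-up appointments".

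The two sets of settings are made differently. The in-clinic fit is verified by real-ear measurement, "with the gain settings adjusted through hearing aid software to meet NAL-NL2 targets" at three input levels (55, 65 and 75 dB). The remote fit is "programmed through hearing aid software to 100% acclimatisation using NAL-NL2 prescription targets for long-term hearing aid wearers", followed by proxy verification in the manufacturer's software. Both then receive the same interview-style adjustment on participant feedback.

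Group allocation says that the clinician who performs follow-ups and assessments is blind to group and order. First and second interventions has that clinician adjust the settings two weeks into each period. The 4FREAR is measured two weeks later.

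**The concern.** Anonymising a file hides whose it is and how it is labelled. It does not hide what it contains, and the content is what the follow-up clinician works on. If the gain pattern, or memory of having made it, points to the fitting method, the clinician is no longer blind when making adjustments that help determine the primary outcome.

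A second route does not depend on knowing the arm. In period 2, a clinician who remembers or can reopen the settings the participant accepted in period 1 could reproduce them. The two final outputs would then look alike whatever the fitting method.

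The trial is described as non-inferiority with a 5 dB limit. Artificial similarity between arms therefore works in favour of the conclusion the trial is set up to reach.

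**Working it through.** The plan gives no figure for blinding, so the check is mainly a comparison of sections.

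**1. What the safeguards cover.** De-identification ({16b}, {17a}) removes labels and identity. Removal of features unavailable remotely (Initial in-clinic hearing aid fitting) equalises which features are present. Neither conceals gain values. The second safeguard also shows that the authors accept that file content can unblind; they close that route for features but not for gain.

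**2. What the follow-up clinician handles.** First and second interventions has this clinician change the settings until the participant is satisfied. The gain settings are what the two methods may leave different: one set was moved to real-ear targets, the other is a software fit with proxy verification.

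**3. Link to the primary outcome.** The abstract's Results paragraph places the 4FREAR comparison after these adjustments, and Primary outcome defines it as the 4FREAR difference. The adjustments are part of the measured quantity.

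**4. Who the clinician is.** {17a} says clinicians know the method at the fitting, before allocation and blinding. This reads as the same clinicians becoming blind later. Group allocation requires only blindness to group and order. No section says that the follow-up clinician or assessor must not have fitted that participant, and one role covers both follow-up and assessment.

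**5. Timing.** Outcomes are at weeks 8 and 14, and each follow-up is two weeks earlier, so at weeks 6 and 12.
- The remote fitting is about 2 weeks after the in-clinic one. The aids are sent 2 weeks after the remote fitting and worn for 2 weeks before follow-up.
- The first follow-up is thus about 2 + 2 = 4 weeks after the remote fitting and 2 + 2 + 2 = 6 weeks after the in-clinic fitting.
- The period-2 follow-up is 12 − 6 = 6 weeks after the period-1 follow-up.
- These gaps weaken a clinician's memory but do nothing about a stored record. No section restricts access to the period-1 end settings during period 2.

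**6. Sensitivity of the conclusion (illustration only).** Assume 54 pairs, a true signed mean difference of 5 dB (at the limit), a one-sided 5% test, and clinician behaviour, not participant preference, bringing the two outputs *b* dB closer. With *s* the SD of the paired difference, which the article does not give:

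P(false non-inferiority) = Φ( *b* / (*s*/√54) − 1.645 )

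| *s* (assumed) | *b* = 0 | *b* = 1 dB | *b* = 2 dB |
|---|---|---|---|
| 4 dB | 5% | 58% | 98% |
| 6 dB | 5% | 34% | 79% |
| 8 dB | 5% | 23% | 58% |

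For example, with *s* = 6 and *b* = 1: 6/√54 = 0.816; 1/0.816 − 1.645 = −0.42; Φ = 0.34. The table shows that small artificial convergence would matter at the limit. It does not show that any occurs.

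**The case against.** The strongest reply is that the protection is real and goes beyond labels. Files are de-identified, features are matched, both fits start from the same prescription at the same acclimatisation level with the same receiver and dome, and both end with the same feedback-led adjustment. The follow-up clinician is stated to be blind to group, and rostering is a detail that an article may leave to the full protocol. Convergence after participant-led adjustment is also partly what the trial studies, so similar final settings are not in themselves bias.

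Much of this stands, and it rules out several stronger readings:

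- A reader might infer that blinding rests on file names alone. It does not; feature matching is a safeguard at content level.
- A reader might infer that the follow-up clinician holds both of a participant's files and can compare them. {16b} says that two files exist, not who can open them.
- A reader might infer that the gains reveal the method. That is not shown. Only real-ear target matching, as against a software fit with proxy verification, separates the two, and later adjustment may blur it.
- A reader might infer that the same person fits and follows up. The article does not say so; it only fails to exclude it.
- A reader might want to quantify loss of blinding by assuming a share of participants whose period-1 settings are copied. The document gives neither that share nor a true difference, and copying needs no knowledge of the arm, so the result would not measure unblinding.

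What the reply does not rescue is the claim in {17a}. The article does not leave the matter to another document: it asserts that the stated mechanism makes the clinician unable to tell. Similarity reached through participant preference is a legitimate result; similarity reached through a clinician's recognition or recall is not, and the design as described cannot tell them apart.

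**Conclusion.** The point holds in a limited form. The assertion that the clinician cannot determine the fitting process is not secured by anonymous storage, even together with feature matching, because the gain settings remain in view of the person who changes them. That person is not required to be someone other than the fitting clinician. Recognition of the arm is plausible, not certain.

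As a separate matter from arm blinding, nothing keeps period-1 end settings from the clinician in period 2, which leaves open a bias towards similarity.

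Both follow-ups of all randomised participants (60 planned) are exposed. The size of any effect on the 4FREAR contrast cannot be derived from the document, and the illustrative probabilities above rest entirely on assumed SDs and shifts. The verdict assumes that the follow-up clinician sees the gain values when adjusting them, which follows from the task described, and that no undisclosed rule separates the roles. If such a rule exists, it should be stated. This should be corrected; it does not invalidate the design.

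**What to change.** Amend Group allocation, Concealment mechanism {16b} and Who will be blinded {17a} to state that:

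- (a) a participant's follow-ups and outcome real-ear measurements are done by an existing clinician who did neither of that participant's fittings;
- (b) the research assistant releases only the active period's settings;
- (c) period-1 session records and end settings are withheld until the week-14 assessment is complete.

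Where (a) cannot be met, (b) and (c) still apply and the double-blind claim should be qualified. Recording the clinician's guess of the method after each follow-up is optional: it documents blinding but does not protect it.

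The cost is rostering and file-access rules, with no extra visits. The downside is some scheduling constraint where few clinicians are available.

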### Procedure for unblinding if necessary {17b}

There is no requirement for unblinding.

## Data collection and management

### Plans for assessment and collection of outcomes {18a}

Primary and secondary outcome measurements will be assessed 4 weeks after each intervention at an in-clinic appointment.

### Plans to promote participant retention and complete follow-up {18b}

All participant appointments will be confirmed 2 weeks and 48 h prior to each appointment. All outcome assessments will be completed in person.

### Data management {19}

Data will be managed through REDCap.

### Confidentiality {27}

Data will be maintained electronically on a secure server at the University of Auckland. The information collected from participants will remain confidential and will be deidentified for analysis purposes.

### Plans for collection, laboratory evaluation, and storage of biological specimens for genetic or molecular analysis in this trial/future use {33}

Not applicable for this study as there are no biological specimens.

## Statistical methods

### Statistical methods for primary and secondary outcomes {20a}

The difference in REAR measures between interventions will be used as the primary outcome. The data will be modelled as a fully factorialised 5-way mixed-measures ANOVA with repeated measured being: ear (right and left), frequency (500, 1000, 2000, 4000 Hz), REM signal input level (55 dB, 65 dB, 75 dB), and fitting method (in-clinic or remote); and level of hearing loss (mild or moderate) as a between-participant factor.

Secondary analyses of speech intelligibility, hearing-related quality of life, hearing aid benefit, sound quality and preference, and speech-in-noise ability will be conducted in the same way. In the analyses, a main or interaction effect involving fitting method will provide evidence that the in-clinic and remote fitting approaches led to differences in the variables involved. Interactions will be explored using testing of simple effects using follow-up ANOVAs and graphical representations of data including error bars based on the standard error of the mean difference between the points, to represent the repeated measured nature of these variables, and using the standard error of the mean for analysis related to level of hearing loss.

Given the statistical power inherent in the data analysis (repeated measures approach), the sample size should be sufficient. To ascertain the clinical importance of the difference observed at a statistical level, a criterion of + / − 5 dB will be applied to REAR measures, in accordance with best practice guidelines. The secondary outcomes do not have a convention associated with clinical importance, so any statistical effects observed will be discussed in terms of the specific measure and meaningful outcomes in previous research as well as making comparisons based on confidence intervals.

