#### Secondary outcomes

Secondary outcome measures include:*Estimated speech intelligibility* measured by the Speech Intelligibility Index (SII) of each hearing aid fitting. An SII of zero indicates no intelligible speech and a score of one indicates all speech information is available to the participant. The REAR allows an SII to be calculated for each signal strength, allowing for comparison between interventions.*Hearing-related quality of life* measured using the Hearing Handicap Inventory for Adults (HHIA), a 25-item questionnaire that measures hearing-related QOL across social and emotional subdomains [27].*Hearing aid benefit* measured using the Abbreviated Profile of Hearing Aid Benefit (APHAB), a 24-item questionnaire that measures hearing aid benefit across four subscales: ease of communication (EC), reverberation (RV), background noise (BN), and aversiveness (AV)*Sound quality and preference* measured on 5-point Likert scales. Participants are asked to rate the overall sound quality of each intervention, and rate their preference between the interventions.*Process acceptability* (how likely the participant is to recommend the process to another person) measured as a net promotor score for each intervention.*Speech-in-noise ability* measured for each intervention with an unaided and aided quick speech-in-noise (QSIN) test. QSIN will be performed according to the QSIN user guide in a calibrated testing room with speech and background noise (four-speaker babble) presented from a single speaker in front of the participant at a level of 65 dB HL. A QSIN score for each intervention will be calculated from the average SNR loss across 3 standard test lists.

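### Preference is one rating between the two fittings, so the fitting-method ANOVA prescribed for it has no fitting-method effect to test

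*Protocol article*

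**What the plan says.** Section {20a} of the protocol article specifies the primary model as a full-factorial five-way mixed ANOVA. Its repeated factors are "ear (right and left), frequency (500, 1000, 2000, 4000 Hz), REM signal input level (55 dB, 65 dB, 75 dB), and fitting method", and it adds "level of hearing loss (mild or moderate) as a between-participant factor". The next paragraph extends this to the secondary outcomes, naming preference among them: "sound quality and preference, and speech-in-noise ability will be conducted in the same way". It also gives the rule for reading the results: "a main or interaction effect involving fitting method will provide evidence that the in-clinic and remote fitting approaches led to differences".

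The section Secondary outcomes describes the item on a 5-point Likert scale: "Participants are asked to rate the overall sound quality of each intervention, and rate their preference between the interventions". Sound quality is thus rated for each intervention, and preference is rated across the pair.

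Under Group allocation, Concealment mechanism {16b} and Who will be blinded {17a}, participants do not know which fitting they are wearing in either period. The allocation records are released by the research assistant once the research is complete.

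**The concern.** A repeated-measures ANOVA tests fitting method by comparing values recorded under each level of that factor. A preference rating is not recorded under a level of fitting method. It is the comparison itself. If such a rating enters the stated model, the only factor that varies is hearing-loss level, a between-participant characteristic. The analysis would then show whether mild and moderate groups answered differently, not whether participants preferred the remote or the in-clinic fitting.

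Blinding adds a step. A participant can express a preference only for the first or second aid worn, or for a masked label, so the raw rating says nothing about method until it is linked to sequence. The article states neither that recoding nor a neutral reference value. At stake is the one secondary outcome in which participants directly compare the two fittings. Its analysis would have to be devised after the allocation is known, because the analysis named for it does not answer the question.

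**Working it through.** **Inputs.** From {20a}: ear (2 levels), frequency (4), input level (3) and fitting method (2) within participants, and hearing loss (2) between. From Secondary outcomes: the structure of each measure. From Sample size {14}: 60 recruited and up to 10% attrition, so 60 × 0.90 = 54 completers. The article states no figure for the preference analysis, so there is none to reproduce.

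**Step 1: size of the stated model.** Repeated cells per participant: 2 × 4 × 3 × 2 = 48. Fixed-effect columns with hearing loss: 48 × 2 = 96. Effects: 2^5 − 1 = 31, of which 2^4 = 16 involve fitting method.

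**Step 2: what each outcome supports.** With k applicable factors, including method, there are 2^k − 1 effects, and 2^(k−1) of them involve method. The rank of the 96-column design was computed for 60 participants under each data structure.

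| Outcome | Values per participant | Factors present | Rank of 96 | Effects | Involving method |
|---|---|---|---|---|---|
| REAR (primary) | 48 | all five | 96 | 31 | 16 |
| SII | 12 | ear, level, method, hearing loss | 24 | 15 | 8 |
| HHIA total, sound quality, aided QSIN | 2 each | method, hearing loss | 4 | 3 | 2 |
| Preference | 1 | hearing loss | 2 | 1 | 0 |

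The SII row assumes a value per ear. The article ties SII to each hearing aid fitting and says "The REAR allows an SII to be calculated for each signal strength, allowing for comparison between interventions", but does not list ear as a factor. APHAB gives 4 subscales × 2 periods = 8 values. Each subscale can be handled like HHIA, or subscale can be added as a factor.

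Every row except the last keeps at least two effects involving method, so the decision rule can be applied. For preference it cannot.

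**Step 3: can the intercept stand in for the method effect?** Centre the 5-point item at its midpoint, so that it runs from −2 (first aid) to +2 (second aid). This scoring is assumed, since the article gives none. Let τ be the mean preference for remote over in-clinic, and π any general pull towards the second aid.

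- Group A (remote first): raw mean = −τ + π
- Group B (in-clinic first): raw mean = τ + π
- Raw mean over equal groups: [(−τ + π) + (τ + π)] / 2 = π

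Without recoding, the intercept estimates the order effect and τ cancels. With the sign reversed in Group A, the two means become τ − π and τ + π, and their average is τ. Recoding by sequence, centring and averaging over sequences together recover the fitting-method effect.

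**Step 4: precision of a suitable analysis.** The 95% CI half-width for a mean in 54 completers is 2.006 × SD / √54. No SD is given, so a range is assumed: SD 1.0 gives 0.27, SD 1.2 gives 0.33 and SD 1.4 gives 0.38 points. This shows that the item can be informative. It does not measure harm from the present wording.

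**The case against.** The best defence has three parts.

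First, the sentence naturally means a mixed ANOVA with fitting method, hearing loss and whichever repeated factors an outcome has. Nobody would put audiometric frequency into a questionnaire model, and a condensed article can leave factor lists to the analysis plan. This stands for SII, HHIA, APHAB, sound quality and QSIN. A reader might infer from the literal wording that the secondary analyses as a whole cannot be fitted. The document does not support that: each of these outcomes has a workable reduced model, and the rule can be applied to it.

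Second, a comparative rating behaves like a difference score, so the ANOVA intercept is the method effect and the hearing-loss term is the method-by-hearing-loss interaction. This is true only after the rating has been recoded by sequence and centred at neutral. The article states neither step, and an intercept is not a main or interaction effect in the sense of the stated rule.

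Third, linking first and second to method is routine at unblinding, and every outcome needs that link. This is fair as to cost. But for the other outcomes the link only labels values that the model already separates, whereas for preference the stated model has no place for it.

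The format of the item is not shown, so one value per participant is inferred from the wording. It is the plain reading of a rating between interventions.

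**Conclusion.** The point holds for preference only. If preference is one comparative rating per participant, the analysis named for it contains no fitting-method effect, tests only mild against moderate hearing loss, and cannot be read by the article's own rule. This is an analysis stated for an outcome that it does not fit, rather than a detail left for later.

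The conclusion would change if the item were in fact scored separately for each fitting, because a reduced fitting-method model would then apply. The wording points the other way.

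Severity is low. One secondary item is affected and the primary analysis is untouched. The wording for the other secondary outcomes is loose but not wrong. Nothing here argues for adding period, sequence or random-effect terms to those models. Balancing over sequences matters for preference because of the order effect shown in the working.

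**What to change.** Remove preference from the sentence that sends all secondary outcomes to the common ANOVA, and add wording such as:

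*Preference will be recoded after unblinding to remote versus in-clinic using each participant's allocated sequence, and centred at the no-preference point. The mean and 95% CI, averaged over the two sequences, will be estimated and compared with zero. Hearing-loss level may be included as a factor.*

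A signed-rank or sign test against the no-preference point, or the proportion preferring each method, is an acceptable alternative for a 5-point item. One of these should be chosen before the allocation records are released.

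For the remaining secondary outcomes, add a clause saying that each is analysed by a mixed ANOVA with fitting method, hearing-loss level and whichever repeated factors that outcome has.

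The cost is a sentence or two of analysis text. No new data, visits or change in sample size are needed.

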### Sample size {14}

Sixty participants (thirty per group) will be recruited for the trial. This will provide 90% power at the 5% significance level to detect an overall clinically meaningful difference of 5 dB 4FREAR and allow for up to 10% attrition.

Power analysis was conducted by selecting a random sample of patients from a clinical register and using the variance in REM scores to estimate the expected variance in the research. Power analysis for a 5-dB non-inferiority limit (the acceptable variance in REMs according to the NZAS Best Practice Guidelines) in a continuous outcome in a non-inferiority trial with an alpha level of 5% and 90% power indicates a total sample size of 54 (27 per group). We propose a sample size of 60, which will allow 30 in each hearing loss group and therefore a repeated measures analysis on groups of 30.

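### All 16 effects that contain fitting method count equally as evidence of a difference, and the main effect, the one that matches 4FREAR, is not made decisive

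*Protocol article*

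**What the plan says.** In the Protocol article, the Results part of the abstract and the Primary outcome section both name one quantity: the difference between the two interventions in the four-frequency average real-ear aided response (4FREAR). Sample size {14} sizes the trial on a 5 dB limit for that quantity and states: "This will provide 90% power at the 5% significance level".

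Statistical methods {20a} sets the analysis: "The data will be modelled as a fully factorialised 5-way mixed-measures ANOVA". The repeated factors are ear (2 levels), frequency (4), input level (3) and fitting method (2), with "level of hearing loss (mild or moderate) as a between-participant factor". The secondary analyses "will be conducted in the same way". The rule for reading the results is that "a main or interaction effect involving fitting method will provide evidence that the in-clinic and remote fitting approaches led to differences". For the interactions, "Interactions will be explored using testing of simple effects using follow-up ANOVAs".

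The same section then brings in a criterion of 5 dB in either direction to judge whether a statistically observed difference in real-ear response matters clinically. It says that the secondary outcomes have no comparable convention. It gives no significance level per test.

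**The concern.** The rule treats the fitting-method main effect and every interaction containing it, up to the five-way term, as equally good evidence that the approaches differ. The design rests on one comparison. The analysis opens many routes to declaring a difference and does not say which one answers the trial's question.

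Two things are at stake. First, with identical fitting methods, some method effect is likely to reach nominal significance by chance, and 11 of the 16 candidates are three-way or higher interactions. Secondly, if the decisive effect is not fixed before the allocation is revealed, choosing among the 16 afterwards can be driven by the data.

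The rule also carries over to the secondary outcomes, several of which lack some of the model's factors. The rating of preference between the interventions is a single comparative answer, so it has no fitting-method factor to test.

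**Working it through.** **The plan's own figures.** The protocol states no overall error rate for the ANOVA, so there is none to reproduce. In the sample size section, 54/(1 − 0.10) = 60 reproduces. The 54 cannot be checked because no SD is given. Under a two-group formula, n per group = 2·SD²·(z for alpha + z for power)²/5², 27 per group implies an SD of about 6.28 dB at one-sided 5%, or 5.67 dB at one-sided 2.5%. Either way, that calculation concerns one comparison.

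**Counting the effects.** Five factors give 2^5 − 1 = 31 effects. Fitting method can be combined with any subset of the other four factors, so 2^4 = 16 effects contain it: 1 main effect, 4 two-way, 6 three-way, 4 four-way and 1 five-way.

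**Chance of at least one nominal finding when the methods are identical**, treating the tests as independent:

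- 5% per test: 1 − 0.95^16 = 0.560.
- 2.5% per test: 1 − 0.975^16 = 0.333.
- One pre-specified test at 5%: 0.05.

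**Does dependence between tests or a sphericity correction change this?** The ANOVA was simulated with no method difference, 4,000 datasets per scenario, half the participants at each hearing-loss level. Each participant had 2 × 4 × 3 = 24 method differences, and all 16 tests were run at 5%. The covariance structures and SDs are assumptions.

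| Assumed structure of the method differences | n = 60, uncorrected | n = 60, Greenhouse-Geisser | n = 54, Greenhouse-Geisser |
|---|---|---|---|
| Compound symmetry | 56.8% | 53.9% | 53.4% |
| Nested variance components | 57.3% | 54.9% | 53.1% |
| Serial correlation over frequency and level, SD rising with frequency | 63.5% | 52.1% | 52.3% |

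All scenarios are above 50%. The 63.5% arises only when non-spherical data are left uncorrected, so it is not used as the size of the problem.

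**Effect of the 5 dB criterion.** In the n = 60 runs, the share with both a significant method effect and any cell mean difference above 5 dB was 0% to 0.5%. This also depends on the assumed SDs.

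**Secondary outcomes.** An outcome with only fitting method and hearing-loss level as factors has 2 effects containing method: 1 − 0.95² = 9.75%. The Speech Intelligibility Index is obtained for each hearing aid and each signal strength, so it keeps ear and input level and has 2^3 = 8 such effects: 1 − 0.95^8 = 33.7%.

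**The case against.** The strongest reply is that a significant effect is not the end of the plan's reasoning. Real-ear differences must still be set against 5 dB, and the protocol's conclusions are framed around clinically significant differences. This stands. A reader might infer that the trial has a better than even chance of falsely reporting an important difference in output; the documents do not support that, and the simulated 0% to 0.5% points the other way. The criterion does not, however, alter the stated rule for what counts as evidence of a difference, and it does not reach the secondary outcomes.

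A reader might also infer that the protocol has no primary contrast. It does name one: the 4FREAR difference. With balanced data, the fitting-method main effect is that difference averaged over ears and input levels. What is missing is a statement that this effect outranks the 15 interactions.

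Nor do the documents promise an overall 5% error rate for the ANOVA that is then broken. The 5% belongs to the sample size calculation, and its use per test here is an assumption. Multiplicity and sphericity corrections are often left to an analysis plan, which is not shown, so their absence from the article is not the point. The point is the rule that the article does state; an unseen correction would lower the error rate but would not say which effect is decisive.

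Finally, the instruction to analyse secondary outcomes in the same manner can fairly be read as the same approach with whichever factors apply. On that reading most of them have far fewer than 16 tests, and only the preference rating does not fit at all.

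**Conclusion.** The point holds as a defect in a stated decision rule. Sixteen effects have equal standing as evidence of a difference, in a trial defined and sized on one. At an assumed 5% per test, the chance of at least one nominally significant method effect under identical methods is about 56% (about 52% to 55% with a sphericity correction under the assumed covariance structures), and 33% at 2.5% per test.

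This is the rate of a false statistical difference in the real-ear model, not of a false clinically important one. Secondary outcomes with only method and hearing-loss level carry about 10% each, with no numerical criterion behind them.

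**What to change.** In Statistical methods {20a}, state that the primary analysis is the fitting-method effect on 4FREAR: the mean of the four frequencies, averaged over ears, at one stated input level or as the mean of the three. Judge it by its confidence interval against the protocol's own 5 dB limit. State that all interactions with fitting method are exploratory.

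For the secondary outcomes, specify a paired model for each, using only the factors that the outcome has. Test the between-intervention preference rating against no preference.

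The change is to wording only and needs no new data or participants; it should be made before the allocation is revealed. The cost is that the interactions lose confirmatory status, so a difference confined to one frequency, ear, input level or hearing-loss level would be reported as exploratory.
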